#### **4.2.3. Informed consent procedure**

The investigators will explain to each patient with central diabetes insipidus or healthy volunteer the nature of the study, its purpose, the procedures involved, the expected duration, the potential risks and benefits and any discomfort it may entail. Each participant will be informed that the participation in the study is voluntary and that he or she may withdraw from the study at any time and that withdrawal of consent will not affect his or her subsequent medical assistance and treatment. The participant will be informed that his or her medical records may be examined by authorized individuals other than their treating physician.

All participants for the study will be provided a participant information sheet and a consent form describing the study and providing sufficient information for participant to make an informed decision about their participation in the study. Enough time needs to be given to the participant to decide whether to participate or not.

The formal consent of a participant, using the approved consent form, will be obtained before the participant is submitted to any study procedure.

The consent form will be signed and dated by the investigator or his designee at the same time as the participant sign. A copy of the signed informed consent will be given to the study participant. The consent form will be retained as part of the study records. Neither patients nor the healthy participants will have a direct benefit from the study. Therefore, as a compensation for their time,

patients and healthy participants will receive a compensation after the study participation of 400 sFr. Additionally, travel costs for patients not living in the area will be reimbursed.

### 4.3. Study procedures

Study participants will present at three separate days at the outpatient study center, Ambulatory Study Center (ASZ), University of Basel (USB). As seen in the figure above, if enrolled in the study patients and healthy volunteers will be randomized to receive either the placebo or MDMA first. After a wash-out phase of at least 2 weeks, the second visit of the study will be planned with either MDMA or placebo. The screening procedure, main visit and telephone interview are described in detail in the following paragraphs:

[figure not shown]

#### 4.3.1. Screening visit

Participants will be informed about all procedures involved in the study. A medical history, physical examination and blood screening will be performed to evaluate eligibility. For detailed information see 4.2.2.

If included in the study, patients or healthy participants will be randomized to receive either first placebo or first MDMA, respectively. Patients or healthy participants, study investigators and study nurses will be blinded to the study intervention. Eligible patients or healthy participants will undergo a detailed psychological baseline evaluation right after the screening at the same day. The psychological baseline evaluation includes the assessment of anxiety level by using the State-Trait Anxiety Inventory (STAI), scoring the mood using the Beck's Depression Inventory (BDI II), the degree of alexithymia using the Toronto Alexithymia Scale (TAS-20) and general health status using the Short Form (36) Health Survey (SF-36). No more than 2 months should be between the screening visit and the main study visit.

#### 4.3.2. Main visit (MDMA or placebo)

During the main visits, participants will present in the morning at the study site. An indwelling intravenous catheter will be placed in an antecubital vein for blood sampling. To avoid clotting participants will receive continuous 0,9% NaCl infusion during the whole visit with a total of maximum of 250 ml (40 ml/h). Patients with central diabetes insipidus and secondary adrenal insufficiency on hydrocortisone (HCT) substitution will be asked to take 50 mg HCT instead of the regular dose for the main visits (30mg morning dose and 20mg noon dose), desmopressin will be taken by the patients as regular.

Pregnancy test /drug screening: The participants will be screened for pregnancy and illicit drugs using a urinary test before starting the session at each visit. Positive screens for stimulants, opioids or tranquilizers will result in exclusion from the study. Positive screens for THC (cannabis) will be recorded but do not result in study exclusion. This is because THC consumption can be detected in urine for up to several weeks and use days before a study day is unlikely to affect the outcome.

Questionnaires: A standardized list of complaints (LC) (see further information below) and the STAI-S will be performed on baseline (timepoint 0min) and repeated at timepoint 180min (STAI-S), timepoint 360min (LC).

Vital parameters: Blood pressure (systolic and diastolic), heart rate and body temperature will be measured at several timepoints during the main visit (timepoint -60 min, 0 min, 30min, 60 min, 90 min, 120 min, 150min, 180min, 210min, 240 min, 270min, 300 min, 330min, 360 min).

Study Drug: MDMA (100mg) or placebo will be administered orally one hours after the start of the main visit.

Subjective effects: Autonomic and subjective/emotional effects will be assessed repeatedly throughout the main visit (timepoint 0 min, 30min, 60 min, 90 min, 120 min, 150min, 180min, 240 min, 300 min, 360 min) using subjective effects questionnaire assessed with visual analog scales (VAS).

Blood samples: Samples will be collected on the study days as shown in Table 2. Blood will be collected to determine OT, MDMA and plasma sodium level at 0 min, 90 min, 120 min, 150 min, 180min and 300 min. Cortisol, prolactin, copeptin and ACTH concentrations will be taken at 0 min, 90 min, 150 min and 300 min. The blood samples will be taken as aliquots for the later batch analysis and will be centrifuged at 4°C at 3000 rpm for 10 min, and then stored at -80°C until analysis. Plasma sodium level will be taken for instant analysis. A basal hormonal status will be

conducted at baseline in main visit 1 at timepoint 0 min including TSH, fT4, IGF1, FSH, LH, Testosterone and Estradiol. Blood concentrations are determined in our laboratory using validated and previously used methods.

Amount of blood sampling: The total amount of blood collected during the study is 310 ml. This amounts to less than a standard blood donation and spread out over a time frame of 8 -10 weeks. The risk is there for acceptable for the participants.

Computer test: At timepoint 150 min during the expected peak concentration of MDMA participants will perform the following tasks: Face emotion recognition (FERT) and multifaceted empathy task (MET). The test will take 25 minutes in total for the participant. See section below for further information.

Standardized meal / fluid intake: The subject will be allowed to drink to thirst – the total fluid intake will be (in addition to 250ml i.v.) recorded during the main visit. We will offer a standardized breakfast and lunch at timepoint -60 min and timepoint 180 min.

End of session: Subjects will be under continuous medical supervision until any alterations of consciousness have completely subsided, this is expected within 6h for MDMA. After the test session subjects are allowed to leave only if the subjective effects have ceased (VAS score “drug effect” back to predose  $\pm$  1) and as assessed by the investigator. No close monitoring is needed beyond this time and subjects can return home as also was the case in a similar study [39, 43, 55].

Subjects are prohibited to drive a car or to operate any machines within 48 h of substance administration. As for any complications resulting from this clinical study the investigators will provide assistance for treatment and the costs are covered by the study insurance. Any AE between sessions will be recorded at the beginning of the next session or telephone interview. Safety follow-up meetings beyond this time are not needed [57]. However, subjects will be provided with the phone number of the study physician, and the study leader in case they need assistance, or should medical problems arise.

Second main visit: After a washout-phase of at least 2 weeks, visit 2 will be scheduled. At Visit 2, participants will undergo the same procedure as described above with the second intervention. In female participants, the main visits will preferentially be planned during the mid-follicular phase or if on estrogen replacement therapy, during the active treatment phase

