#### **3.2. Primary and secondary endpoints**

The primary endpoint is the area under the concentration time curve in OT level from baseline OT measurement (before intake) to 6 hours after a single administration of MDMA (100mg) as compared to placebo in the same subjects between patients with central diabetes insipidus and healthy volunteers.

Secondary outcomes will be assessed between MDMA as compared to placebo for patients with central diabetes insipidus and healthy volunteers:

- A. Peak change in OT plasma level
- B. Time course of plasma OT levels
- C. Time course of plasma MDMA concentration
- D. Time course of cortisol, prolactin, copeptin and ACTH levels
- E. Subjective/emotional effects assessed on a 10-point visual analog scale (e.g., feelings of anxiety, pleasure, fear)
- F. Recognition of negative emotions in the face emotion recognition task (FERT)

- G. Empathy in the multifaceted empathy task (MET)
- H. Anxiety level with the State-Trait Anxiety Inventory (STAI)
- F. Level of Alexithymia using the Toronto-Alexithymia-Scale 20 (TAS-20)
- G. Level of depression using the Beck-Depressions-Inventory II (BDI-II)
- H. Level of general physical & mental health using the short form health survey (SF-36)
- I. Safety: Assessments of clinical/laboratory variables (blood pressure, heart rate, body temperature, plasma sodium)

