## **5 STATISTICS AND METHODOLOGY**

### **5.1. Statistical analysis plan and sample size calculation**

The null hypothesis is that the area under the concentration time curve of OT is equal for patients with central diabetes insipidus and healthy volunteers after a single dose of MDMA, i.e. the primary endpoint is zero. The alternative hypothesis is that the area under the concentration time of OT is lower in patients with central diabetes insipidus as compared to healthy volunteers, i.e. the primary endpoint is not zero.

The time course of OT measures after intake of MDMA and placebo will be visualized by means of line plots and boxplots for patients with central diabetes insipidus and healthy volunteers. Summary statistics (median, interquartile range, minimum and maximum value) will be presented for each measurement time of OT for MDMA and placebo for patients with central diabetes insipidus and healthy volunteers. Maximum OT time will be summarized for MDMA and placebo for patients with central diabetes insipidus and healthy volunteers separately by means of frequency distribution according to the measurement times, and by median, interquartile range, minimum and maximum value. OT area under the concentration time curve from baseline to 6 hours after intervention will be tested for a difference between MDMA and placebo for patients with central diabetes insipidus and healthy volunteers. Summary statistics (median, interquartile range, minimum and maximum value) will be presented separately.

All other secondary endpoints will be analyzed descriptively. The time course of MDMA, cortisol, prolactin, copeptin, and ACTH levels will be visualized by means of line plots and boxplots, and summary statistics will be presented for each measurement time for MDMA and placebo for patients with central diabetes insipidus and healthy volunteers separately.

Sample size was estimated in order to show a significant increase in OT after the intake of a single oral dose of MDMA with a power of 90 % and a significance level  $\alpha$  of 0.05. Sample size estimation was based on preliminary data from 28 healthy adults. In this trial, OT levels following MDMA intake was studied. The mean increase in OT levels for MDMA was 809+/-64 pg/mL and 259 +/- 62 pmol for placebo.

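### Cortisol and ACTH are summarised for all patients together, although those on hydrocortisone take it on both sampling days, so the pooled patient curves cannot be read as a response to MDMA

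*Protocol*

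**What the plan says.** Protocol section 4.3.2 foresees a subgroup described as "Patients with central diabetes insipidus and secondary adrenal insufficiency on hydrocortisone (HCT) substitution". On the main visits these patients "will be asked to take 50 mg HCT instead of the regular dose for the main visits (30mg morning dose and 20mg noon dose"). At the second main visit "participants will undergo the same procedure as described above with the second intervention", so the instruction applies on both the MDMA and the placebo day.

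The same section fixes the blood sampling: "Cortisol, prolactin, copeptin and ACTH concentrations will be taken at 0 min, 90 min, 150 min and 300 min". Section 3.2 makes this secondary endpoint D: "Time course of cortisol, prolactin, copeptin and ACTH levels", assessed as MDMA against placebo in patients and in healthy volunteers.

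Section 5.1 fixes the presentation. Each hormone's course over time is to be drawn in line plots and boxplots. For the figures that go with these plots, the section lays down that "summary statistics will be presented for each measurement time for MDMA and placebo for patients with central diabetes insipidus and healthy volunteers separately". The statistical part of the synopsis says the same. Neither place divides the patients by hydrocortisone use.

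Under section 4.1, any adult up to 65 with confirmed central diabetes insipidus can enter as a patient, and no exclusion criterion concerns hydrocortisone. Volunteers may take no medication except hormonal contraception.

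**The concern.** Hydrocortisone is cortisol. In a patient who has taken it, the measured cortisol is a mixture of administered drug and whatever the patient secretes. In secondary adrenal insufficiency the ACTH drive is deficient by diagnosis, and hydrocortisone can suppress it further. A patient curve that combines such patients with patients whose axis is intact, and stands beside a curve from volunteers who take no hydrocortisone, has no clear meaning. A raised cortisol level might come from the drug. A small difference between MDMA and placebo might come from the proportion of users. The plan gives the reader no way to tell these apart from an effect of MDMA.

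What is at stake is the interpretation of the cortisol and ACTH parts of one secondary endpoint.

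**Working it through.** **Inputs.** Section 4.3.2 gives the hydrocortisone amounts, the start of the visit in the morning, study drug one hour after the start, and cortisol and ACTH samples at 0, 90, 150 and 300 min. The synopsis gives 15 patients (taken here to be the diabetes insipidus group). The protocol does not give the clock time of arrival, the clock time of the morning hydrocortisone, the regular dose, or the number of users. These are treated as unknown or varied over a stated range.

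**Step 1: the plan's own figure.** 30 mg + 20 mg = 50 mg. The stated total is reproduced.

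**Step 2: where the noon dose falls.** With arrival at hour a, study drug is given at a + 1. Noon is then (12 − (a + 1)) × 60 minutes after study drug. Arrival times of 07:00 to 09:00 are assumed.

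| Assumed arrival | Noon, min after study drug | 300-min sample, min after noon | Samples after noon |
|---|---|---|---|
| 07:00 | 240 | 60 | 300 min |
| 08:00 | 180 | 120 | 300 min |
| 09:00 | 120 | 180 | 150 and 300 min |

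Throughout this range the 300-min sample follows the noon dose. Table 2 places lunch at 180 min, which fits the middle row. The morning dose has no clock time; if it is taken at or before arrival, it precedes all four samples.

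**Step 3: what is mixed.** Section 5.1 summarises levels by time point and treatment. At each time point the patient summary combines users, whose cortisol includes the drug, with non-users, whose cortisol does not. Nothing cancels in these per-treatment curves, because each treatment is shown on its own.

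**Step 4: the within-patient difference.** The hydrocortisone instruction is the same on both days, so the drug contribution largely drops out of MDMA minus placebo. What remains is dilution. Let k of 15 patients be users, let δ be the mean MDMA-minus-placebo cortisol change in non-users, and let users respond at a fraction r of δ. Then

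pooled mean change = δ × [1 − (k/15) × (1 − r)].

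With r = 0 (users have no response of their own, the extreme assumption) this is δ × (1 − k/15):

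- k = 3: 1 − 3/15 = 0.80
- k = 6: 1 − 6/15 = 0.60
- k = 9: 1 − 9/15 = 0.40
- k = 12: 1 − 12/15 = 0.20

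From k = 8, users are the majority of 15, so under the same assumption the median change would come from a user. If r is above 0, the dilution is smaller.

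**Step 5: reach.** No sample-size, power or error-rate figure depends on any of this.

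**The case against.** The strongest reply has four parts.

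*The crossover deals with it.* Both days carry the same hydrocortisone, and the secondary outcomes are framed as MDMA against placebo within each group. This stands in part: a within-patient difference is largely free of the drug. But section 5.1 plans levels per treatment, not differences, and the difference would still be diluted.

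*The endpoint is only descriptive.* No test or between-group estimate is planned for cortisol or ACTH, and the dilution figures concern a mean change that the plan does not list. This stands, and it limits the severity. Patient and volunteer curves will still appear side by side and be compared by eye.

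*A split can be left to the statistical analysis plan.* That would be fair if the protocol were silent. It already specifies the display, by two groups only, and that display cannot be interpreted for these two hormones.

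*A low ACTH response in this population is real.* This is true, and it is why users should be shown separately and not dropped.

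Some stronger readings are tempting. A reader might infer that patients take extra hydrocortisone, but the text says 50 mg in place of the regular dose and does not state that dose. A reader might infer that the ACTH curve shows the drug. Hydrocortisone is not ACTH, so the curve shows deficiency or suppression. A reader might also infer a false blunted response whose size depends only on the number of users. Timing, absorption and the response in non-users matter as well.

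**Conclusion.** The point holds for the planned display. As written, the pooled per-treatment cortisol and ACTH curves for patients cannot be read as a pituitary-adrenal response to MDMA, and they are not comparable with the volunteers' curves. For cortisol this follows from the administered drug; for ACTH it follows from the underlying deficiency or its suppression.

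The size cannot be fixed from the protocol, because the number of users is not given. The range of 0.80 to 0.20 for 3 to 12 users among 15 assumes no response at all in users, and it applies only to a mean within-patient change. The timing of the 300-min sample rests on assumed arrival between 07:00 and 09:00.

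It would be wrong to conclude that the trial's main result is affected. The primary endpoint is the oxytocin area under the curve, and neither it nor the sample size depends on this. The point is minor.

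**What to change.** In section 5.1 and the matching synopsis text, state that patient cortisol and ACTH summaries and plots will be presented separately by hydrocortisone use, that the number of users will be reported, and that any comparison with healthy volunteers will be limited to patients not on hydrocortisone. The endpoint list in section 3.2 can stay as it is. No change to any dose is proposed.

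The cost is one or two sentences. The downside is small subgroups: with 15 patients, either one may hold only a few, so individual curves may say more than quartiles. Fixing the split before data are seen avoids a later choice that could look driven by the results.

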| Risk / Benefit Assessment      | 
Risk: Single dose administration of MDMA has been studied frequently and proven to be safe in healthy subjects. The main expected acute adverse effects are consistent with moderate sympathomimetic toxicity including moderate hypertension, tachycardia and a raise in body temperature. Acute psychological distress was observed to be minimal. A slight depressed mood lasting up to three days after MDMA application has been observed. The patients will be monitored closely during MDMA application and until the acute effects wear off. Participants will receive a phone call 3 days after the intervention to assess mood changes.
 
Benefit: We do not expect immediate benefit to the study participants. Our data could provide a potential provocation test for oxytocin and clarify whether patients with diabetes insipidus have an oxytocin deficient state.
                                                                                                                                                                                                                                                                                                                                                                                                                                                                                                                                                                                                                                                                                                                                                                                                                                                                                                                                                                                                                                                                                                                                                                                                                                                                                                                                                                                                                                                                                                                                                                                                                               |

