### **3.4. Study intervention**

MDMA will be prepared as gelatin capsules containing 25 mg of pharmaceutically pure MDMA hydrochloride (ReseaChem GmbH, Burgdorf, Switzerland) and mannitol filler. Placebo will be prepared as identical gelatin capsules containing only mannitol filler. All products are prepared

by a Swissmedic-approved GMP facility (Apotheke [name], Biel, Switzerland) according to GMP guidelines and with the authorization of the BAG.

MDMA will be administered in a single dose of 100 mg (4 capsules of 25 mg MDMA). The MDMA dose was chosen based on previous studies using oral administered MDMA with dosages between 75mg and 125mg [43–46]. In controlled clinical [30-47] setting MDMA is considered to be safe with moderate subjective and cardiovascular effects [44, 48]. The peak effects of MDMA are expected after 2 h [44, 48–50].  $T_{1/2}$  of MDMA (100 -125 mg dose) is about 8-10 h [44, 51]. Effects of MDMA last about for 6 h [44].

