#### **4.3.3. Telephone interview**

Based on previous studies experience no formal follow-up support is needed but we will perform a telephone interview. 3 days after the main visits, patient or healthy participant will receive a phone call to inquire for Adverse Events using:

- A. The List of complaints e.g. sleeping problems, dry mouth, dizziness, palpitation, tremor, nausea, headache, transient anxiety and concentrating difficulties.
- B. Adverse Events that are not recorded by the LC e.g. subjective signs of depressed mood, psychosomatic problems, psychological problems and any perceptual disturbance e.g. flash backs.

The schedule of events for a subject is shown on **table1**

|                                         |                                          | SCREENING
VISIT | VISIT 1
MDMA/PLACEBO | VISIT 2
MDMA/PLACEBO | TELEPHONE
INTERVIEW
1 and 2 |
|-----------------------------------------|------------------------------------------|--------------------|-------------------------|-------------------------|-----------------------------------|
| Informed consent & Eligibility criteria |                                          | x                  |                         |                         |                                   |
| Questionnaires / Examination     |                                          |                    |                         |                         |                                   |
| Medical history questionnaire           |                                          | x                  |                         |                         |                                   |
| General physical examination            |                                          | x                  |                         |                         |                                   |
| ECG / standardized blood pressure       |                                          | x                  |                         |                         |                                   |
| Psychiatric interview (DSM IV)          |                                          | x                  |                         |                         |                                   |
| Questionnaires                          | Short Form 36 Health Survey (SF 36)      | x                  |                         |                         |                                   |

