The main expected acute adverse effects are consistent with moderate sympathomimetic toxicity including moderate hypertension, tachycardia and a raise in body temperature. Patients and healthy participants will be screened with an ECG and standardized blood pressure measurement; any pathological finding will be assessed by the study physician. Closer monitoring will be implemented if blood pressure values exceed 180/120 mmHg systolic blood pressure ( $P_{\text{sys}}$ ). Treatment of a hypertensive reaction ( $P_{\text{sys}} > 220$  mmHg) may include administration of oxygen, nitrates and nifedipine, or esmolol and/or transfer to medical services (Emergency Department). In the case of angina pectoris, oxygen is given, and ECG monitoring is initiated, and cardiac enzymes will be measured followed by consultation with the cardiologist on call. Cardiac arrest triggers immediate cardiopulmonary reanimation and defibrillation by the study team (defibrillator on site) and call to the ambulance (0144). An increase in body temperature of 0.5°C are expected after MDMA administration [43, 72, 73]. If body temperature rises by more than 1.5°C appropriate treatment including hydration and cooling will be initiated [56].

Ecstasy use has been associated with both dehydration and hyperhydration leading to hyponatremia [56, 74–77]. Subjects will be encouraged to drink to thirst, but in general no less than 1 and no more than 3 l during one session. Serum sodium levels checked as described in Table 2 at timepoint 0min, 90min, 120min, 150min, 180min and 300min. If symptoms of hyponatremia such as confusion or vomiting present between these intervals, subjects will be further examined and sodium levels rechecked. Participants will be informed of these symptoms and encouraged to report if these symptoms occur following the study visit.

Acute psychological distress was observed to be minimal; no lasting biological or psychological injury is expected. There is no indication that administration of MDMA in a controlled setting has any adverse effects on cognitive function [30, 72, 85].

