Recreational use of Ecstasy has been linked to reversible neurotoxicity [78, 79], especially when the drug is taken frequently and in high doses [80]. In contrast, imaging studies do not indicate any changes after moderate MDMA use [35]. Several studies document no lasting effects of Ecstasy in moderate Ecstasy users [53, 78, 81]. No changes in serotonin transporter density were seen using positron emission tomography and [11C]-McN5652 four weeks after MDMA

administration (1.5-1.7 mg/kg) in MDMA-naive human volunteers [86,87]. The use of MDMA in controlled settings is considered safe with regard to neurotoxic effects [47, 82].

MDMA has rarely been associated with liver toxicity but often under overdose and not in controlled clinical setting [56]. Liver enzymes will be measured at the screening visit and pathological results will be excluded regarding the exclusion criteria.

The participants will be under continuous medical supervision and closely monitored during MDMA application and until the acute effects completely subsided; expected within 6h for MDMA [74]. Subjects with known risk factors for future drug abuse including current major depression, psychotic disorder and anxiety disorders [83] and prior drug dependence or other relevant illicit drug use [84] will be excluded from the study. Illicit drug use will also be monitored during the study using repeated urine drug screens before both main sessions.

Six hours after stimulation participants will be allowed to return to their home alone. If effects persist, the night is spent at the research facility. In the case of unexpected prolonged or severe adverse reactions subjects will remain in the hospital and are monitored as long as necessary. Subjects will be provided with the phone number of the study physicians in case of an emergency between/after study sessions.

MDMA is expected to produce sequelae (1-3 days post MDMA) including difficulty concentrating, irritability, or slightly depressed mood in about 10% of subjects [69]. Participants will receive a phone call 3 days after the intervention to assess mood changes and adverse events.

MDMA is neither mutagenic nor teratogenic and their chronic use is not associated with birth defects. Pregnant women are excluded from the study and pregnancy tests will be done before each test session. Effective birth control will be mandatory for female participants.

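### The ban on driving and operating machines ends at a fixed 48 h, although the protocol expects after-effects, possibly including difficulty concentrating, for up to three days after MDMA

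*Protocol*

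**What the plan says.** The driving rule stands in Protocol section 4.3.2, in the text on the end of the session: "Subjects are prohibited to drive a car or to operate any machines within 48 h of substance administration". It depends on time alone, and no condition lengthens it.

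The after-effects are described in section 7.2: "MDMA is expected to produce sequelae (1-3 days post MDMA) including difficulty concentrating, irritability, or slightly depressed mood in about 10% of subjects". The synopsis, under Risk / Benefit Assessment, gives a matching duration for one of these symptoms: "A slight depressed mood lasting up to three days after MDMA application has been observed".

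Other provisions on effects that persist:

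- Section 4.3.2 has a symptom-based rule for leaving the site on the session day: "After the test session subjects are allowed to leave only if the subjective effects have ceased".
- Section 7.2 provides an overnight stay if effects persist, and a longer hospital stay after unexpected prolonged or severe reactions.
- Sections 4.3.2 and 7.2 give participants a telephone number for the study physician. Section 4.3.2 also states that no further safety follow-up meetings are needed.
- Section 6.2 has a noticed clinical abnormality treated and followed until it resolves or stabilises.
- Section 4.3.3 schedules a telephone interview 3 days after each main visit. It uses, among other things: "The List of complaints e.g. sleeping problems, dry mouth, dizziness, palpitation, tremor, nausea, headache, transient anxiety and concentrating difficulties".

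**The concern.** The protocol names a symptom that could bear on driving, expects it in a window that reaches day 3, and then ends its only driving precaution at 48 h whether or not the symptom is still there. A participant who cannot concentrate properly on the third day is free to drive as far as the protocol text goes. The scheduled call that would pick this up comes after the restriction has lapsed, and no consequence for driving is attached to the answer.

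What is at stake is participant safety, on a small scale. The endpoint, the analysis and the validity of the comparison are untouched.

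**Working it through.** The protocol gives no figure to reproduce here, so the check compares the stated times and then sizes the group concerned.

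**Inputs**

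- Length of the ban: 48 h from administration (section 4.3.2).
- Sequelae window: 1-3 days, in about 10% of subjects, for three symptoms taken together (section 7.2).
- Scheduled contact after discharge: day 3, about 72 h (sections 4.3.3 and 7.2).
- Participants exposed to MDMA: at least 30 (section 5.2). The design is a cross-over, so every completer receives MDMA.
- MDMA half-life 8-10 h, effects about 6 h (section 3.4).

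**Step 1: ban against window.** The 1-3 days can mean the days on which symptoms occur or how long they last. On either reading the upper end is about 3 x 24 = 72 h. Uncovered time = 72 - 48 = 24 h at most.

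**Step 2: ban against acute effect.** Half-lives elapsed at 48 h: 48/10 = 4.8 to 48/8 = 6. Fraction of drug remaining: 2^-4.8 = 3.6% to 2^-6 = 1.6%. Against the stated effect duration, 48/6 = 8 times. The ban is ample for the acute effect, so the gap concerns after-effects only.

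**Step 3: how many participants.** Expected number with any listed sequela = 30 x 0.10 = 3. The chance of at least one such participant = 1 - 0.90^30 = 0.958. If only 24 participants are counted (assuming that the 12 evaluable subjects of section 5.1 are per group), the figures are 24 x 0.10 = 2.4 and 1 - 0.90^24 = 0.920. These are expected counts, not maxima, and they cover all three symptoms over the whole window. The protocol does not split the 10% by symptom or by day, so the number with difficulty concentrating after 48 h cannot be derived and may be zero.

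**Step 4: does another provision close the gap?** The discharge rule and the overnight stay act on the session day. The hospital stay is for unexpected prolonged or severe reactions, not for an expected mild sequela. The physician's telephone number and the follow-up in section 6.2 give access to individual advice, but neither mentions driving. The day-3 interview asks about concentration about 72 - 48 = 24 h after the ban has ended. None of them extends the ban.

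**The case against.** The strongest reply is that the two statements are compatible. One is a precaution, the other a forecast of mild after-effects, and nothing in the protocol says that these after-effects impair driving. Section 7.2 also states: "There is no indication that administration of MDMA in a controlled setting has any adverse effects on cognitive function". Section 3.4 says of the acute phase: "Effects of MDMA last about for 6 h", and 48 h is generous against that. A reader might therefore infer from this point that participants are knowingly allowed to drive while impaired, or that sections 4.3.2 and 7.2 contradict each other. The documents support neither inference. They do not link the sequelae to driving ability, and they do not say how many participants have any symptom after 48 h.

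Two further points stand. Section 4.2.3 says: "All participants for the study will be provided a participant information sheet and a consent form". That sheet was not available for this review and may already tell symptomatic participants not to drive, so no claim can be made that participants go unadvised. And a participant who feels unwell can phone the study physician at any time.

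The objection does not remove the mismatch itself. The general statement on cognitive function stands in the same section as an explicit expectation of difficulty concentrating, and a precaution should follow the explicit expectation. Telephone access depends on the participant thinking to ask, whereas the driving rule as written tells them that the restriction is over.

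A ban lasting until every symptom has gone would itself be a poor rule. Section 2 notes that patients with hypopituitarism often have residual symptoms despite treatment. Without a pre-dose reference, such a patient could be restricted indefinitely for reasons unrelated to MDMA.

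**Conclusion.** The point holds as a low-severity precaution. The fixed 48 h limit falls up to 24 h short of the symptom window that the protocol itself states, and no provision in the protocol text makes the ban depend on symptoms. About 3 of 30 participants would be expected to have some listed sequela. How many of them would have difficulty concentrating after 48 h is unknown, possibly none.

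This rests on reading the upper end of the window as about 72 h, on the 10% figure applying to this population, and on the protocol text alone. If the participant information already carries the advice, all that remains is to bring the protocol into line with it.

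**What to change.** In section 4.3.2, reword the rule to apply after each session, since both are blinded. Driving and operating machines are prohibited for at least 48 h. If difficulty concentrating or another impairing symptom that is new or worse than before dosing is still present at 48 h, the prohibition continues until the symptom has resolved or the study physician clears the participant, by phone or at the day-3 call. Check the participant information and align it if it does not already say this.

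The reference to the pre-dose state keeps chronic symptoms from triggering an extension, and clearance by the study physician gives the extension an end.

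The cost is wording only: no added visit, since clearance uses the existing telephone number or the planned call. The downside is about 24 h more restriction for participants still symptomatic at 48 h whose symptoms end by day 3, and longer only for those whose symptoms outlast that. Because the rule also covers the placebo session, someone with a new symptom then would be restricted too. Participants without such symptoms are unaffected.
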